#### Program fidelity

In addition to the program-level data described here, we also collect project data via fidelity assessments, program surveys, and the program level core assessment battery (PL-CAB). Each program completes a fidelity assessment to determine the components of coordinated specialty care (CSC) provided using the First Episode Psychosis Services Fidelity Scale (FEPS-FS) [51], a standardized measure of fidelity to EP program best practices. Similar to the fidelity assessments, program surveys and the PL-CAB assess various components offered through the CSC program, program census, and staffing. The data from these other sources may also be used to inform the analysis of the program-level data.

### Data collection timeline

Participants, support persons, and EP program staff complete CAB clinical outcomes surveys at treatment baseline and every six months throughout treatment in the EP program. EP program staff also enter data at the time of the service user’s discharge from the EP program. Survey windows and due dates are all tied to the survey baseline date that program staff enter for each service user. For our purposes, the survey baseline date is associated with a service user’s start of care in their program, not when they are enrolled in Beehive. Though different programs may use a different visit during the early phase of engagement in clinical care as the anchor for the survey baseline date, all the service users within any given clinic use the same type of clinical visit as the baseline benchmark.

Beehive survey windows span several months each to facilitate the completion of the CAB. The baseline window in Beehive starts at the survey baseline date and ends 4 months later. Subsequent follow-up windows are due every six months from the survey baseline date. The follow-up windows open two months before the due date and close 4 months after the due date (Fig. 3). Programs are encouraged to complete surveys as close to the due date as possible, but flexibility is given to accommodate delays in clinical visits or unexpected barriers to completion of the survey (i.e., service user crisis or hospitalization). Data collection continues every six months throughout a service user’s treatment.

**Fig. 3 Fig3:**
[figure not shown]
Beehive survey windows

### Sample size

Our estimated sample size is based on each EP program’s estimate of new clinical intakes in their program per year. We estimate that we will be able to systematically collect outcomes data on approximately 500 FEP service users and 300 additional CHR service users over the course of the study. Our target sample size for the barriers and facilitator interviews is 30 providers and 30 service users, or at the point where the main themes meet saturation. There are also additional participants in EPI-CAL from various focus groups, qualitative interviews, surveys outside of Beehive, and fidelity assessments.

### Data collection methods

EPI-CAL researchers consulted the Guidelines for Data Acquisition, Quality and Curation for Observational Research Designs (DAQCORD) [52] on the design and implementation of this protocol to achieve a high-quality data set. Whenever possible, DAQCORD indicators were implemented through Beehive. We will highlight our implementation of several DAQCORD indicators below. See Supplementary Table S2 for the full list of DAQCORD indicators and how they have been implemented in this study.

Regarding the DAQCORD indicator of internationalization, Beehive and the EPI-CAL CAB will be localized into 12 threshold languages to meet the requirements of operating in California Medicaid (Medi-Cal) clinics. The languages will include English, Spanish, Vietnamese, Mandarin, Cantonese, Farsi, Armenian, Hmong, Khmer (Cambodia), Korean, Russian, and Tagalog. All measure translations go through either back-translation or translation by committee.

The majority of survey data collected for EPI-CAL is collected directly from service users and their support persons through Beehive and is described in the outcomes section. We designed Beehive to facilitate service users and support persons completing these surveys independently, though we encourage clinical staff to support individuals as needed (e.g., answering questions about survey content). There are some outcomes that require clinical staff to input data into Beehive (e.g., diagnosis, service use) and several outcomes of interest (e.g., symptoms, functioning, suicide risk) are collected from multiple respondent types.

Regarding the DAQCORD indicator to test data collectors and provide them with feedback regarding the accuracy of their performance across all relevant study domains, EPI-CAL clinical psychologists oversee the training of program staff who will complete the COMPASS-10 [48] and Global Functioning: Social [44] and Role [43] scales. Individuals either attend the live training or can watch a recording of it. Program staff must then provide a rating for 10 vignettes and must score within 1 point of the gold standard rating for each vignette to pass. We provide feedback for incorrect answers and allow program staff to retake the test with a different set of vignettes if needed.

### Data management

For data collected outside of Beehive, including program census information collected to assess the feasibility of implementing an LHCN, data are collected from programs and entered into an Excel document and stored on a HIPAA-compliant cloud storage.

Regarding the EPI-CAL CAB, since participants enter survey data directly into Beehive, data entry by research staff is not required. Most data cannot be edited or modified after it is entered. For example, after the first survey has been completed about a service user, the survey baseline date can no longer be modified by the user. Any requests to change this field must be approved and implemented by the research team so that they can ensure all data are automatically assigned to the appropriate time point by the application. Additionally, surveys are in a read-only state after they have been completed by any type of survey respondent (service user, primary support person, and clinical team).

The database is hosted on Amazon Web Services (AWS) cloud. Amazon’s Simple Storage Service (Amazon S3) is used for storing content, logs, and backup data. This allows versioning, secured storage, and retrieval. Server-side data encryption is managed using AWS S3. Report functionality in Beehive allows data to be saved as a .csv file. The research team can access data across all programs but have access to only a limited data set. The only protected health information (PHI) that the research team has access to is a service user’s zip code, month and year of birth, and dates of service. When data is exported from Beehive by the research team, it is stored according to UC Davis policies for storage of PHI.

Because the data collection is happening in the context of regular clinical service, EP programs also have access to the data from their own program. Access to data is restricted based on user permissions managed by the EP programs. When programs download data from Beehive, it is their responsibility to treat the data as sensitive data and protect that data according to federal and state regulations and institutional requirements.

Information about all variables is documented in a data dictionary. The data dictionary documents: (a) variable name, (b) date of implementation for each translation, (c) a description of the data stored under the variable name, (d) the type and format of data (e.g., numeric, date MM/DD/YYYY), (e) implemented data validation, (f) response options when relevant, (g) missing data code, (h) validly skipped data code, (i) scoring information, and (j) details about skip logic when relevant. The data dictionary is updated whenever changes are made to the database, for example when new variables or new translations of existing variables are added.

Data validation is built into the data collection process in Beehive. Whenever possible, data collection has been designed to avoid free text fields so that data validation can be implemented. Some examples of data validation implemented in Beehive data collection are (a) minimum and maximum values for numeric text entry data, (b) formats for dates and zip codes, etc., (c) restriction on certain response options that are part of select-multiple questions (e.g., cannot select “none of the above” and select any other option).

### Data analysis

Prior to analysis, we will complete descriptive summaries for all data collected in Beehive, including service user and clinician demographics, survey completion for each survey at each timepoint, and survey scores for quantitative measures. The distribution and completeness of each analysis variable will be examined to determine appropriateness of different statistical methods. The availability of within-person longitudinal data will be reviewed to determine whether longitudinal or cross-sectional approaches are most appropriate. Descriptive summaries will be generated for each clinic individually, as well as network wide.

To address Aim 1, we will examine whether we achieved adequate enrollment in Beehive by using descriptive statistics to see if at least 70% of eligible participants and 50% of their available support persons across the network were enrolled and completed at least one survey timepoint. To approximate the number of total service users eligible for enrollment, we will pull the total census number from each program annually. Eligible service user participants are defined as those who are determined eligible to receive care at each program. Available support persons are defined and identified by the service user. Service users must have completed their EULA to be considered enrolled. For the analysis, we only consider individuals who have agreed to share data with the University of California, Davis (UCD) as “enrolled”, but service users can decline this option and still use their data within their program for clinical purposes. Just like service users, primary support persons are not considered enrolled unless they have agreed to share data with UCD. Service users and support persons can make different choices regarding their data sharing permissions, i.e., a service user can decline to share their data for research purposes while a support person can opt-in. For the feasibility analysis, we will only examine what proportion of enrolled service users also have an enrolled PSP, acknowledging that there may be more enrolled PSPs whose corresponding service user opted out of data sharing. Survey data analysis procedures for clustered data (treating EP programs as clusters) will summarize characteristics of enrolled service users who complete enrollment and at least one survey. Enrollment rates (with 95% confidence interval) will be computed for (1) all eligible service users and (2) potentially available support persons. For the latter, we will report, for the denominator of eligible service users with available support persons, what proportion of those service users had at least one support person complete a baseline or 6-month survey assessment.

To assess Aim 2, the adoption of Measurement-Based Care (MBC), we will first examine the degree of use of data in care between the pre- and post-implementation periods of the project. Before Beehive implementation in each EP program, providers complete pre-implementation surveys about their demographic information (age, sex, race, ethnicity) and professional characteristics (years of education, degree type) and complete questionnaires on their (1) beliefs about the utility of data in care planning and (2) skills in discussing data with service users. Compared to the pre-implementation period, we hypothesize that providers will report a change in the use of data to determine treatment choices after training and using the app for at least one year. Separate models will be fit for each of the primary and alternative operationalization of Beehive clinician-usage metrics as the exposure variable of interest. Adoption of data in care will also be measured by examination of whether a service user’s treatment team lead examined completed surveys from service users. To determine the degree to which providers are actively viewing data collected in Beehive, research staff will review the Beehive survey reports variable that shows whether or not each survey has been viewed by the service user’s treatment team lead (binary yes/no). We hypothesize that EPI-CAL treatment team leads will have viewed service user data collected through Beehive in at least 50% of cases. Lastly, we will examine whether the clinician reported that Beehive data impacted the treatment plan as assessed by the in-app queries periodically presented to EP provider users.

Through the qualitative work that was completed in the first phase of this project [24], a variety of key outcomes were identified by our program, service users, and support person workgroups. Psychiatric symptoms, quality of life, and functioning were prioritized as key outcomes by all types of respondents and our analysis will center on these domains. When examining group-level differences, it is important to note that there is not a “Beehive” and “not Beehive” group of service users; all service users are assigned to the Beehive group and thus no analysis can examine the effect of Beehive use in treatment compared to a typical control group. Instead, to assess the impact of utilizing MBC in an EP LHCN (Aim 3), we will analyze a dataset consisting of one record per service user per follow-up assessment timepoint and outcomes expressed as within-person change scores from baseline (for continuous measures) or as count or binary outcomes. For count or binary outcome data, the corresponding baseline value of the outcome will be included as a person-level covariate, when appropriate. Outcomes will be measured by the MCSI, personal wellbeing index (PWI), and functioning measures (Global Functioning Social and Role Scales (GF: S and GF: R) or Mental Illness Research, Education, and Clinical Center (MIRECC) version of the Global Assessment of Functioning (GAF) scale) for each of the six-monthly assessment timepoints during the first 24 months. Continuous outcomes will be transformed into within-person change scores from the baseline assessment for each follow-up assessment. Data are structured hierarchically; there is nesting of measurements from service users, who are nested within clinicians within EP programs. Therefore, for continuous, binary, and count outcomes, generalized linear mixed models will be used to estimate the adjusted effects of exposures on the key outcomes of interest, adjusting for a parsimonious set of other clinician- and service user-level covariates. Random effects will be specified for sites, with additional effects specified for clinician and service users’ contribution to the model fit, according to the Schwarz Information Criterion.

A key operationalization of the exposure indicator will be based on a composite indicator for any review of the service users’ completed surveys. In particular, this variable will be scored a 1 for a given service user in a given follow-up assessment if the treatment team lead reviewed the service users’ completed survey data. The comparison groups are defined by clinician metrics from Beehive aggregated over the 6-, 12- and 18-month assessment period, and the primary analysis is based on a composite indicator for any review of the service users’ survey data by the treatment team lead. We will also assess timepoint-specific changes in psychotic symptom severity for each of the half-yearly assessment timepoints during the first 24 months, with the primary analysis based on a time-varying indicator for any endorsement of “impact on treatment plan” on the in-app queries as a time-varying independent variable.

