To determine if implementation of the LHCN leads to an increase in the delivery of measurement-based care (Aim 2), providers will complete self-report questionnaires in the pre- and post-implementation period of the project. To examine adoption of a new technology in the EP program, we will compare providers with respect to their self-reported use of data to determine treatment choices at two timepoints: prior to Beehive implementation, and then after training in and use of Beehive. Pre- Beehive implementation surveys include Treatment Alliance and Use of Data in Care Planning in reference to specific service users. Providers will also complete the Comfort with Technology survey. The sampling frame for each site will consist of surveys about service users of currently enrolled EP providers, restricted to service users with at least six months under treatment and who had been seen in the preceding month. Beehive training materials will then be implemented consistently across participating EP programs; implementation efforts will highlight the utility of data to identify treatment goals and metrics of improvement during treatment planning and provide guidance on service user-centered ways to collaboratively review data and monitor progress during care. Then, in post-implementation, the same set of surveys are administered to EP programs who have implemented Beehive in their program for at least a year. The survey sampling strategy used in the pre-implementation period to select clinician-service user pairs will be repeated after Beehive has been implemented in the clinic for a full year, to ensure a valid pre/post comparison on this outcome. Due to expected turnover from the clinician side and discharge/exit from the program on the service user side, we will not be able to sample the same group from the pre-implementation period. However, there will most likely be some representation in the post-implementation period from respondents who participated in the first phase of surveys. Therefore, these are not completely independent samples, nor are they completely repeated samples.

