To determine the extent to which providers utilize the Beehive platform to deliver measurement-based care (Aim 2), we adopt two different approaches. First, we will examine whether a service user’s treatment team lead reviews completed surveys in Beehive, which is recorded by the application. During service user registration in Beehive, EP providers designate the service user’s treatment team lead, typically their primary clinician. Once a survey respondent completes a survey in Beehive, the data are immediately available to view in the Beehive dashboard. The Beehive survey reports will include a variable that shows whether or not each survey has been viewed by the service user’s treatment team lead (binary yes/no). Research staff will use this data to determine the degree to which providers are actively viewing data collected in Beehive.

To explore how Beehive data are used by those who frequently utilize the application, two types of in-app queries were developed: urgent clinical issues and data-use questions. Urgent clinical issues are a type of notification (in-app and email) in Beehive that encourages EP staff to review service user data. These notifications trigger if, during registration or survey completion, a service user endorses risk-to-self or risk-to-others on the Modified Colorado Symptom Index (MCSI) [26], the intent to stop taking their medication [27], or lack of a permanent address. Beehive displays urgent clinical issues on a dashboard widget and to resolve them, users must indicate how they used the data in care. Additionally, an in-app query is presented to the service user’s treatment team lead every ten visits to the service user’s data page. Data-use questions assess (1) if the data was reviewed during a session with the service user or support persons and, if yes, (2) how the data was used as part of care.

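### The only model stated for the Aim 2 pre/post question takes Beehive usage as its exposure, which is not observed before Beehive, so it does not estimate the period change

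*Protocol article*

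**What the plan says.** The contrast is set out twice in the protocol article. Under Outcome measures and instruments, providers are compared on self-reported use of data at two timepoints: "prior to Beehive implementation, and then after training in and use of Beehive". Under Data analysis, Aim 2 begins with use of data across the pre- and post-implementation periods, and "we hypothesize that providers will report a change in the use of data to determine treatment choices" once they have trained on the application and used it for at least a year.

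The model follows directly: "Separate models will be fit for each of the primary and alternative operationalization of Beehive clinician-usage metrics as the exposure variable of interest". It is the only sentence in the Aim 2 analysis that specifies a model. The section adds two further Aim 2 assessments: whether treatment team leads viewed survey data (at least 50% of cases expected), and what clinicians report in the in-app queries.

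The viewing metric comes from the application: "The Beehive survey reports will include a variable that shows whether or not each survey has been viewed". The in-app queries are likewise generated by use of Beehive.

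On sampling, Outcome measures and instruments defines the pre-implementation frame site by site. For the post period, "the same set of surveys are administered to EP programs who have implemented Beehive in their program for at least a year". Of the two sets of respondents it says that "these are not completely independent samples, nor are they completely repeated samples".

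**The concern.** The question is about period: do providers report a different use of data after implementation than before it? The exposure in the stated model is something else, namely how much a clinician used Beehive. An analyst who followed the Aim 2 text literally would fit a model whose main coefficient does not answer the Aim 2 hypothesis. It could miss a real change that all providers share. It could also report a positive coefficient when nothing changed, only because clinicians who open the dashboard already rated themselves higher on using data. The pre/post comparison is the part of Aim 2 that bears on whether the network leads to more measurement-based care, since the other two assessments have no pre-implementation value to compare with.

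**Working it through.** The article gives no sample size, effect size or test level for this comparison, so there is no figure to reproduce. The check sets the passages side by side and then works an illustration on assumed inputs.

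**Does the exposure fit the hypothesis?**

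- Contrast required (Outcome measures and instruments; Data analysis, Aim 2): post-implementation versus pre-implementation.
- Exposure stated (Data analysis, Aim 2): Beehive clinician-usage metrics.
- Source of those metrics (Outcome measures and instruments): views and queries logged by Beehive, so none can be observed in the pre period.
- Mixed models elsewhere in Data analysis: introduced for Aim 3 and for service-user outcomes, continuous ones as change from baseline. They are not written for the Aim 2 provider surveys.
- Where a usage exposure does fit (Data analysis, Aim 3): "The comparison groups are defined by clinician metrics from Beehive aggregated over the 6-, 12- and 18-month assessment period".

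**What would the stated exposure estimate?** Assume equal numbers of pre and post records and outcome SD 1. Let p be the share of post records with usage, δ the true period change for everyone, and g a standing difference between clinicians who use Beehive and those who do not, present in both periods. Usage itself has no effect.

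*Usage coded 0 before Beehive, both periods pooled.*
- Mean of records with usage: δ + g.
- Mean of records coded 0: [p·g + (1 − p)·δ] / (2 − p).
- Usage coefficient (the difference): [δ + 2(1 − p)·g] / (2 − p).

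*Post records only.* The usage coefficient is g, and δ cancels.

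*Period as exposure.* The coefficient is δ.

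With p = 0.5:

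| Assumed truth | Usage, pooled | Usage, post only | Period |
|---|---|---|---|
| δ = 0.30, g = 0 | 0.30/1.5 = 0.20 | 0 | 0.30 |
| δ = 0, g = 0.4 | 0.4/1.5 = 0.27 | 0.40 | 0 |

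One simulated data set for the first row (2,000 records per period) gave 0.24, 0.05 and 0.31. The standard errors of the two usage coefficients are √(1/1000 + 1/3000) = 0.037 and √(1/1000 + 1/1000) = 0.045, so both lie within sampling error of the exact values.

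If every post record shows usage (p = 1), the pooled coefficient equals δ, but only because a binary usage indicator is then the period indicator under another name. A model holding both terms cannot be fitted (design matrix rank 2 for 3 columns).

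**Who is in each period?** The post survey is limited to programs with at least a year of Beehive, and no matching limit is stated for the pre sample. Suppose pre-only programs stayed in the pre mean. With f their share of the pre sample and d their baseline gap in SD below the other programs, the apparent change with no true change is f × d. For assumed f of 10% to 30% and d of 0.2 to 0.8, this runs from 0.10 × 0.2 = 0.02 SD to 0.30 × 0.8 = 0.24 SD. The sign reverses if those programs start higher. The article gives neither f nor d.

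**The case against.** The strongest reply is that this is a misplaced sentence. It names no outcome, and its vocabulary of operationalizations and clinician metrics is that of Aim 3. The period contrast is stated clearly in two places, and an analysis plan that is not shown may hold the right model. Much of this stands: displacement from Aim 3 is plausible, and the algebra above shows what the sentence would do if followed, not what the investigators intend. It does not remove the point. The sentence follows the Aim 2 hypothesis immediately and is the only model given there. The complaint concerns an exposure that the article states, not detail that it leaves out.

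Three stronger readings are tempting, and the article does not support them.

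- *Aim 2 goes untested.* The two-timepoint contrast is declared, and Aim 2 has two other assessments that do not depend on this sentence.
- *The pre/post test will have wrong standard errors.* No independent-samples test is proposed. The article acknowledges the partial overlap, uses clustered-data procedures for Aim 1 and hierarchical models for Aim 3. Leaving the Aim 2 error structure to a fuller plan is not a fault in a condensed article.
- *Programs that fail or leave will inflate the change.* Nothing says that pre-only programs stay in the contrast. The sampling is to be repeated in each clinic after a full year so that the comparison is valid, which can be read as clinic by clinic. Programs short of a year may simply have started late.

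**Conclusion.** The point holds in a limited form. As printed, the only model stated for Aim 2 has an exposure that does not exist in the pre period, and no stated model estimates the change that the article hypothesizes. This follows from the text and needs no numerical assumption. The size of the error if the sentence were followed depends on assumed inputs. In the two cases worked, a true change of 0.30 SD appears as 0.20 (pooled) or 0 (post only), and no true change appears as 0.27 or 0.40. If all post records show usage, the pooled coefficient happens to be right. Whether the sentence is an intended model or a displaced one cannot be settled from the article, and either way it should be corrected. The difference in how the two samples are defined is a reason for a safeguard only, since the size and direction of any resulting bias cannot be known from the document.

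**What to change.** - For the Aim 2 pre/post question, make implementation period (post versus pre) the exposure and the provider-reported use-of-data score the outcome. Include program effects and a random intercept for clinician, so that clinicians seen once and clinicians seen in both periods contribute together.
- Allow the change to differ between programs, by a program-by-period random effect or program-clustered standard errors. Beehive is introduced program by program, and without this the standard error for a network-wide change would be too small if programs respond differently.
- Move the usage-metric models to Aim 3, or label them a post-period-only secondary analysis.
- As a safeguard, base the main contrast on programs surveyed in both periods, and list the others with the reason (late start, withdrawal or other). With program fixed effects this changes the estimate little, but it makes clear which programs the result describes.

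The cost is wording in the analysis section, with no new data. The small downside is that pre-only programs leave the main contrast, although they carry no information on within-program change.

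### For Aim 3 exposures scored per follow-up, a single random-effects coefficient blends within-person and between-person contrasts, so stable traits that affect both data use and change can look like a benefit of measurement-based care

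*Protocol article*

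**What the plan says.** All of this stands in the protocol article under Data analysis.

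- The Aim 3 data set holds "one record per service user per follow-up assessment timepoint", at six-monthly assessments over the first 24 months, so up to four records per person.
- On the outcome scale: "Continuous outcomes will be transformed into within-person change scores from the baseline assessment for each follow-up assessment". The baseline value is promised as a covariate only for count and binary outcomes.
- On the model: "generalized linear mixed models will be used to estimate the adjusted effects of exposures on the key outcomes of interest", with a short, unlisted set of clinician and service-user covariates. "Random effects will be specified for sites, with additional effects specified for clinician and service users’ contribution to the model fit", as judged by the Schwarz criterion.
- On survey review by the treatment team lead, "this variable will be scored a 1 for a given service user in a given follow-up assessment if the treatment team lead reviewed" the completed survey. The next sentence, however, says: "The comparison groups are defined by clinician metrics from Beehive aggregated over the 6-, 12- and 18-month assessment period".
- Symptom change at each half-yearly timepoint is to be analysed "with the primary analysis based on a time-varying indicator for any endorsement of" an effect on the treatment plan in the in-app queries.

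The text names no person mean of the exposure, no centring and no within-person analysis. It states openly that there is no conventional control group.

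**The concern.** An exposure that varies across one person's records carries two kinds of information. One compares a person's exposed and unexposed intervals. The other compares people who are often exposed with people who rarely are. A random-effects model with one exposure term pools the two. That is valid for the within-person effect only if exposure frequency is unrelated to the person's random effect.

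The article gives reasons to doubt this. Under Outcome measures and instruments, a lead can view only surveys that have been completed, so exposure depends on the service user's engagement. The query about use of the data appears after every ten visits to the data page, so a recorded impact depends on how heavily the lead uses the application. Engaged service users and diligent leads may well go with better change anyway, and covariates such as degree level or years of experience (Discussion) help only as far as they capture those traits.

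Aim 3 asks whether measurement-based care goes with significant improvement. A significant single coefficient would not show whether it reflects what happens when data are used or which people have their data used.

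**Working it through.** The article gives no effect size, SD or intraclass correlation for Aim 3, so there is no stated figure to reproduce. From the article come four follow-ups, change-score outcomes, the model class, the MCSI range and about 800 service users expected to give outcomes data. Every SD, trait effect and exposure rate below is an assumption. The true exposure effect is 0 unless stated otherwise, and negative values are a false benefit.

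**Closed form.** Let u ~ N(0,1) be an unmeasured trait, P(exposed) = p = 1/(1+exp(−a·u)), and MCSI change = −b·u + program (SD 2) + person (SD 6) + residual (SD 7), with T = 4. For a random-intercept model:

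- between-person slope = −b·Cov(u,p)/Var(x̄), where Var(x̄) = Var(p) + E[p(1−p)]/T
- shrinkage λ = 49/(49 + 4·(36 + 4 + b²))
- weight on the between-person slope = T·Var(x̄)·λ / {(T−1)·E[p(1−p)] + T·Var(x̄)·λ}

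For a = 1 and b = 2, numerical integration gives E[p(1−p)] = 0.2066, so Var(p) = 0.25 − 0.2066 = 0.0434.

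- Var(x̄) = 0.0434 + 0.2066/4 = 0.0951, and Cov(u,p) = 1 × 0.2066.
- Between-person slope = −2 × 0.2066/0.0951 = −4.35.
- λ = 49/225 = 0.218.
- Weight = (4 × 0.0951 × 0.218)/(3 × 0.2066 + 4 × 0.0951 × 0.218) = 0.083/0.703 = 0.118.
- Single coefficient = 0.118 × (−4.35) = −0.51 points, with a true effect of 0.
- Standard error ratio, within-person to single = √(0.703/0.620) = 1.065.

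The same formulas give −0.27 at a = 1, b = 1 and −1.02 at a = 1.5, b = 3.

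**Simulation under the same assumptions** (1,000 data sets per scenario, a = 1 or 1.5, b = 1 to 3, 280 or 560 people as illustrative sizes). The single coefficient averaged −0.27 to −1.14. At a nominal 5%, it was significant in 9 to 59% of data sets (280 people) and 13 to 81% (560 people). The within-person coefficient averaged −0.02 to 0.03, with about 4 to 6% significant.

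**Second simulation, different assumptions** (800 people, 80 clinicians, residual SD 6, person SD of change 5, half of the trait at clinician level, 60 runs each, so Monte Carlo error near 5% is √(0.05 × 0.95/60) = 0.028):

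| Trait | Single coefficient (significant) | Within-person (significant) | Person mean | No random effects |
|---|---|---|---|---|
| none | −0.01 (8%) | −0.02 (7%) | 0.06 | 0.00 |
| affects level only | −0.02 (3%) | −0.04 (5%) | 0.27 | 0.08 |
| 2 points on change, log-odds 1 | −0.34 (20%) | −0.04 (3%) | −4.29 | −1.66 |
| 2 points on change, log-odds 2 | −0.56 (48%) | 0.02 (5%) | −4.48 | −2.43 |
| 4 points on change, log-odds 1 | −0.58 (62%) | −0.04 (5%) | −8.92 | −3.40 |

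The implied between-person weight is (single − within)/(person mean − within). In the last three rows it is 0.07, 0.13 and 0.06. Without random effects it is 0.38, 0.54 and 0.38. Dropping the service-user effect, which the Schwarz criterion permits, therefore makes matters worse. The last column also omits site effects, so it is an extreme case.

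**Baseline severity as the trait.** If high baseline scores prompt review (level SD 8, occasion SD 7, log-odds 0.5 to 1 per SD, no baseline covariate), regression to the mean alone gave −0.43 to −0.97, significant in 13 to 76% of runs. The within-person term stayed near 0.

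**The case against.** **The split could be in an unseen analysis plan.** A condensed article may leave parameterisation to it. That is possible. Still, the article fixes the model class, the random effects and a single time-varying independent variable, and that specification has the property shown above.

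**Some of Aim 3 is a between-group comparison by design.** Outcome measures and instruments plans adjusted between-group differences in change to 12 months, and the review composite may be aggregated over the 6-, 12- and 18-month assessments. If it is constant per person, nothing is mixed and no within-person term exists; what remains is ordinary confounding. This stands and limits the point to exposures scored per follow-up.

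**Change scores already help.** They remove traits that shift only the level, as the second row of the table shows. A reader might infer that any fixed trait biases the result; the planned outcome scale rules that out.

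**The within-person term is not safe by itself.** A reader might infer that Aim 3 should rest on it alone. The article does not support that. Surveys become viewable only after completion, and alerts triggered by risk answers on the MCSI prompt staff to review, so exposure can follow the very outcome being analysed. With log-odds of review rising by 0.25 per residual SD of current symptoms (560 people, a = 1, b = 2, true effect 0), the within-person coefficient was +1.7 (99% significant) and the single one +1.1 (91%). With carry-over (true effect −3, persisting once exposed, a = 1, b = 0), they averaged −1.05 and −1.26. The near-nominal error rates above hold only because those simulations contain neither mechanism.

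**The claim is one of association.** That is how Aim 3 is worded, but the same section also speaks of adjusted effects and of assessing impact, so the distinction matters for interpretation.

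**Conclusion.** The point holds for the indicator of impact on the treatment plan, which is explicitly time-varying, and for lead review wherever it is scored per follow-up. With an unassigned exposure, the single coefficient mixes two contrasts, and stable unmeasured traits that affect both data use and change can appear as benefit. The illustrative size is about 0.3 to 1.1 MCSI points with a true effect of 0, and more if the service-user effect is dropped. The mechanism follows from the model. The size and false-positive rates rest on assumed SDs, trait effects and exposure rates, and selection in the opposite direction would hide a benefit instead.

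The documents do not show that such traits operate, nor that all of Aim 3 is affected. The sizes of 280 and 560 are not projections from the article: its figure of about 800 is already the number expected to give outcomes data, and its 70% is an enrolment target among eligible service users. The change is worth making before analysis because it is cheap and makes the result interpretable.

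**What to change.** For each Aim 3 exposure scored per follow-up:

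1. Enter two terms, the service user's mean exposure over follow-ups and each follow-up's deviation from that mean, with assessment timepoint as a factor.
2. Keep the service-user random effect regardless of the Schwarz criterion.
3. Report both coefficients and whether they agree. Do not attribute an improvement to measurement-based care when it appears only in the between-person term.
4. Define exposure as data use before the follow-up outcome is measured, so that review prompted by the same survey does not count.
5. State that the split does not remove time-varying confounding or carry-over.
6. State whether lead review is scored per follow-up or aggregated to one value per person. If aggregated, describe it as a between-person association.

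This needs one more model term, a few sentences and no new data collection. The standard error of the within-person coefficient was about 4 to 14% larger than that of the single coefficient across the runs, and 21 to 30% larger when leads' habits were very stable (a = 3 to 4). Service users whose exposure never varies inform only the between-person term.
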